### 2.15. Statistical Analysis

The analyses will follow a prespecified statistical analysis plan using R software (version 4.4.3; R Foundation for Statistical Computing, Vienna, Austria). The continuous variables will be summarized as mean (SD) or median (IQR) according to the distribution, and the categorical variables as n (%). The distributional assumptions for the continuous variables and change scores will be assessed by histogram and quantile–quantile plots, supplemented by a Shapiro–Wilk test. Effect estimates will be accompanied by 95% confidence intervals where appropriate. The clinical analyses will be exploratory because the single-arm design has no concurrent comparison group.

The primary outcome will be reported as a proportion with a 95% confidence interval. Participants with a documented toileting-related fall before loss to follow-up will remain event positive; those without a documented event who discontinue before completing the 6-month ascertainment will have an incomplete primary outcome status rather than be classified as event free.

Nighttime toileting-related and total recurrent falls will be summarized as counts and person-time rates. A negative binomial regression with the log follow-up time as an offset will be the primary event rate model. Adjusted exploratory models will include the center as a random intercept when stable; if sparse events or non-convergence prevent estimation, the observed counts and person-time rates with confidence intervals will be reported descriptively.

The continuous secondary outcomes with applicable paired baseline/Month 6 measurements will be summarized as the within-participant change with 95% confidence intervals and analyzed using paired t tests or Wilcoxon signed-rank tests according to the change-score distribution. Additional repeated observations will be analyzed with linear or generalized mixed-effects models accounting for the within-participant correlation.

Potential center effects will be examined explicitly. The primary cumulative incidence estimate and key implementation outcomes will first be reported for the overall cohort, with center-specific estimates and confidence intervals presented descriptively. When a clustering adjustment is required, the center will be incorporated as a random intercept if a stable estimation is possible. If not, it will be included as a fixed categorical effect where feasible; otherwise, center-specific descriptive estimates will be used. The center findings will characterize implementation heterogeneity and will not be formal rankings of institutional performance.

The implementation and fidelity indicators will also be summarized by center type to characterize the variation across levels of care, without inferring differential effectiveness.

Exploratory multivariable models will use covariates prespecified a priori on clinical grounds rather than data-driven stepwise selection: age, sex, baseline fall history, comorbidity burden, baseline functional status, caregiver support, recruitment setting, baseline urinary symptom status, and predominant disability/functional impairment profile. Model complexity will be limited according to sample size and available event counts to reduce overfitting; participating centers will be included as a random intercept when stable estimation is possible.

Prespecified subgroup analyses will examine age (18–64 vs. ≥65 years), predominant impairment profile (physical/mobility, cognitive, or mixed/multidomain), recruitment setting, baseline urinary symptoms, and functional dependency. Subgroup estimates will include 95% confidence intervals; regression-based heterogeneity analyses will be exploratory when data permit, with no claims of differential effectiveness.

The RE-AIM and intervention fidelity outcomes will be summarized according to their prespecified operational definitions using frequencies, proportions, and 95% confidence intervals where appropriate, overall and by center. The risk–intervention concordance, fidelity deviations, assessment completion, intervention delivery, data completeness, and follow-up completion will be reported transparently. Intervention exposure will be described by the intervention domains and components received, initiation and delivery, adherence where applicable, and major modifications during follow-up, both overall and, where informative, by center and relevant participant subgroups. Because intervention assignment and intensity will be individualized according to clinical indications, the exposure analyses will remain descriptive and will not be used to infer causal treatment effects.

Enrollment, follow-up completion, and evaluability will be reported separately with reasons for loss and missing data patterns. For the primary outcome, extreme-case sensitivity bounds will alternatively classify participants with incomplete 6-month status and no prior documented toileting-related fall as event positive or event negative. The continuous secondary outcomes will use available paired measurements with missingness reported.

No multiplicity adjustment is planned for exploratory clinical or subgroup analyses. Tests will be two-sided, with an emphasis on effect estimates and 95% confidence intervals.

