### 2.12. Outcome Measures

#### 2.12.1. Primary Outcome

The primary outcome will be the 6-month cumulative incidence of at least one toileting-related fall, defined as a fall while going to, using, transferring on/off, or returning from the toilet. It will be calculated as the proportion of participants with ≥1 such fall among those with an evaluable 6-month outcome status and interpreted as event occurrence rather than causal effectiveness (Table 5).

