### 2.14. Sample Size and Enrollment Target

A total of 300 participants are planned to be enrolled, consistent with the registered target. This target refers to participants enrolled and does not imply that all 300 will necessarily have evaluable 6-month outcome data because some loss to follow-up is anticipated.

Because the study is primarily designed to evaluate implementation of a complex individualized pathway rather than superiority of a single treatment against a concurrent control group, no treatment-effect-based sample size calculation was used. The pragmatic target supports multicenter implementation and reasonably precise estimation of key proportions. For an evaluable sample of 300, a simple binomial approximation gives a maximum 95% confidence interval half-width of about 5.7 percentage points for a proportion near 50%, with narrower intervals farther from 50%.

No cluster design effect inflation was applied because this is not a cluster-randomized comparative trial and a reliable intraclass correlation is unavailable. Center clustering will instead be addressed in the prespecified analyses, with center-specific estimates reported descriptively.

With a 10%, 15%, or 20% loss to follow-up, approximately 270, 255, or 240 participants would remain evaluable, corresponding to maximum 95% confidence interval half-widths of about 6.0, 6.1, or 6.3 percentage points for a proportion near 50%.

The numbers enrolled, completing follow-up, and included in each analysis will be reported with reasons for loss or non-evaluability. Center and subgroup analyses will be descriptive, not separately powered tests of differential effectiveness.

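### The primary proportion keeps dropouts who fell and removes dropouts who did not, so it is biased upward if loss is unrelated to falls

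*Protocol article*

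**What the plan says.** Section 2.12.1 of the protocol article defines the primary outcome as the "proportion of participants with ≥1 such fall among those with an evaluable 6-month outcome status".

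Section 2.15 then settles who is evaluable, with one rule for each kind of dropout:

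- "Participants with a documented toileting-related fall before loss to follow-up will remain event positive".
- By contrast, "those without a documented event who discontinue before completing the 6-month ascertainment will have an incomplete primary outcome status", and the protocol says they are not to be counted as event free.

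The stated sensitivity analysis, also in 2.15, is that "extreme-case sensitivity bounds will alternatively classify participants with incomplete 6-month status and no prior documented toileting-related fall as event positive or event negative".

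Section 2.14 anticipates the loss: "With a 10%, 15%, or 20% loss to follow-up, approximately 270, 255, or 240 participants would remain evaluable". Section 2.11 provides for monthly contacts and records the date of each fall. Section 2.15 already uses follow-up time for the secondary fall counts, through an offset in a negative binomial model. Neither the outcome definition nor the analysis section mentions death.

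**The concern.** Declining to call a fall-free dropout event free is sound. The difficulty is the pairing. Of two participants lost in Month 4, the one who fell in Month 2 is in both numerator and denominator, and the one who had not fallen is in neither. Losing fall-free participants shrinks the denominator while the events among the lost are kept, so the ratio rises even when dropping out has nothing to do with falling. Analysing only completers, or using a Kaplan-Meier estimate, would be unbiased in that benign case; the mixture of the two rules is not.

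Section 2.2 makes this incidence the primary clinical objective, and the Conclusions say the estimates will guide later comparative studies. With a single arm the bias cannot cancel in a comparison. It also grows with loss, so the center-specific estimates planned in 2.15 would differ partly because centers lose different shares of participants.

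**Working it through.** **Plan's own figures.** The half-width at 50% is 1.96 × √(0.25/n). For n = 300, 270, 255 and 240 this gives 5.66, 5.96, 6.14 and 6.33 points, which matches the 5.7, 6.0, 6.1 and 6.3 in section 2.14.

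**Inputs.** Enrolment of 300 and loss d of 10%, 15% or 20% come from section 2.14. The protocol gives no expected fall incidence, so the true 6-month risk p is assumed over 10% to 50%. Hazards are taken as constant and loss as independent of falls.

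**Formulas** (time in units of 6 months):

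- Fall hazard a = −ln(1 − p); loss hazard b = −ln(1 − d).
- Fall seen before loss: E = a/(a + b) × [1 − exp(−(a + b))].
- Completes without a fall: C = (1 − p)(1 − d).
- The plan's proportion tends to E/(E + C). The bounds are E and 1 − C.

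**Example, p = 20% and d = 20%.** a = b = 0.2231, so E = 0.5 × (1 − 0.64) = 0.180 and C = 0.64. The plan's proportion is 0.180/0.820 = 22.0%, and the bounds run from 18.0% to 36.0%.

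| True risk | Reported at 10% loss | at 15% | at 20% |
|---|---|---|---|
| 10% | 10.5% | 10.8% | 11.1% |
| 20% | 20.9% | 21.4% | 22.0% |
| 30% | 31.2% | 31.9% | 32.6% |
| 40% | 41.4% | 42.2% | 43.0% |
| 50% | 51.5% | 52.3% | 53.2% |

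The bias runs from +0.5 to +3.2 points. Loss times spread uniformly over the 6 months give nearly the same result (true 30%, 20% loss: 32.7%).

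**Simulation** (300 participants, 4,000 runs, simple normal-approximation interval). At a true 30%, coverage of the nominal 95% interval is about 93%, 91% and 87% at 10%, 15% and 20% loss. At a true 20% with 20% loss it is about 90%. One minus Kaplan-Meier averages 20.0% at a true 20%, and 29.9% to 30.0% at a true 30%.

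**Where the excess comes from.** In the example, 1 − 0.820 = 18% of participants are lost without a fall. With independent loss, their remaining risk is (0.20 − 0.18)/0.18 = 11%. Dropping them is equivalent to giving them the plan's own 22.0%, as if their observed fall-free months had not happened. The same arithmetic shows when the sign changes: if their true remaining risk exceeded 22.0%, the plan's figure would be too low.

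**Deaths** (mortality assumed, no other loss). Take a fall hazard corresponding to 30% and exclude fall-free deaths as incomplete. With 5% mortality the actual cumulative incidence is 29.3% and the reported figure 30.6%; with 10% they are 28.6% and 31.2%.

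**The case against.** **The outcome is labelled exploratory.** No test, threshold or go/no-go rule hangs on it, and section 2.14 says the study is designed mainly to evaluate implementation. At a true 20% the bias is 0.9 to 2.0 points, against half-widths of about 4.8 to 5.2 at that risk. This stands, and it limits the severity. It does not make the estimator right.

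**A reader might infer that the result will certainly be inflated and that a time-to-event estimate is the unbiased figure.** The documents do not support either claim, because they say nothing on how loss relates to falls. In a frail cohort the same people may fall more and drop out more. Suppose half the cohort has 10% risk and 5% loss, and half has 30% risk and 35% loss (assumed values). The truth is 20.0%, the plan gives 20.8% and Kaplan-Meier 19.1%, so here the plan is closer. The time-to-event estimate is still the better default, because it is correct under the simplest assumption and uses the observed fall-free time, but it needs its assumption stated.

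**The bounds already deal with incompleteness.** They contain the truth in every scenario computed under independent loss, and the protocol promises to report reasons for loss. Catch-up of missed contacts and caregiver reporting should also reduce incomplete status. But the bounds treat someone lost in Month 5 like someone lost on day 1, and they leave the headline figure and its interval as they are.

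**A reader might infer that the plan has decided to exclude deaths.** It has not: death is simply not mentioned, and the separate analysis plan may cover it. Nor is a deceased participant's status automatically known, since a fall between the last monthly contact and death may go unrecorded. What can be said is that, under the only rule given, a fall-free death would be incomplete, excluded, and event positive in the upper bound.

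**Conclusion.** The point holds as a should-fix. The two stated rules make evaluability depend on the outcome. If loss is unrelated to falls, the reported proportion is too high by about 0.5 to 3 points at the protocol's own loss rates, and its interval undercovers. The upper end needs 20% loss together with an assumed true risk of 40% or more; at lower risk or lower loss the bias is nearer 1 to 2 points. The sizes rest on assumed fall risks and constant hazards. If loss is related to falls, the net direction cannot be told from the documents. The remark on deaths is an inference from the absence of a rule.

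One related inconsistency: the 270, 255 and 240 evaluable participants in section 2.14 leave out everyone lost, whereas the rule in 2.15 keeps those who fell first. At a true 30%, 300 × (E + C) gives about 275, 262 and 249.

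**What to change.** In sections 2.12.1 and 2.15, define the primary estimate as the 6-month cumulative incidence from time to first toileting-related fall in all enrolled participants, censored at the last completed surveillance contact, with a 95% confidence interval. Use Kaplan-Meier, or Aalen-Johansen with death as a competing event if deaths occur. State that the estimate assumes loss is unrelated to falls given the observed data.

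Keep the crude proportion and the extreme-case bounds as sensitivity analyses. In the bounds, treat a death as event free only where fall status up to death has been ascertained, so that the upper bound remains a worst case. Say also how a fall reported after the last completed contact is handled: counting it while censoring everyone else at that contact would bring back a small version of the same asymmetry.

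The cost is a short text change and slightly more analysis. Fall dates and monthly contacts are already collected, so no new data are needed. Section 2.18 reports that recruitment had not begun on 1 August 2026, so the change can be made before any outcome is seen.

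### The test for four secondary outcomes is chosen from the observed change scores, so the reported change is not fixed in advance, and neither candidate test accounts for center

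*Protocol article*

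**What the plan says.** Section 2.12.2 of the protocol article lists six secondary outcomes. Two are fall counts. The other four are changes from baseline to Month 6 in OABSS, average nocturia episodes per night, POMA and MBI.

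For these four, section 2.15 says that results will be "summarized as the within-participant change with 95% confidence intervals". The rule for testing follows in the same sentence: the outcomes are to be "analyzed using paired t tests or Wilcoxon signed-rank tests according to the change-score distribution". Distributions are to be "assessed by histogram and quantile–quantile plots, supplemented by a Shapiro–Wilk test", and no decision threshold is given. Continuous variables in general are "summarized as mean (SD) or median (IQR) according to the distribution". The text does not say whether the reported change is a mean, a median or a pseudo-median.

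On center, section 2.14 declines a design-effect inflation and says that clustering will be handled in the analyses instead. Section 2.15 then says: "When a clustering adjustment is required, the center will be incorporated as a random intercept if a stable estimation is possible". It adds fallbacks (a fixed center effect, then description only) and a center intercept in the exploratory multivariable models. It does not say when an adjustment counts as required, and it does not connect any of this to the paired comparisons.

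On missing data, section 2.15 says: "The continuous secondary outcomes will use available paired measurements with missingness reported". The extreme-case bounds are stated for the primary outcome only.

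**The concern.** The paired t test and its interval concern the mean change. The signed-rank test concerns the pseudo-median, the median of all pairwise averages of the change scores. The two agree when change scores are symmetric and separate when they are skewed. A rule that picks one after the data are seen leaves the estimand open. One scale could be reported as a mean change and the next as a pseudo-median. Because the article puts its emphasis on estimates and confidence intervals, the quantity being estimated matters more here than the p value.

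Skewed change is plausible in this study. Section 2.14 aside, section 2.8 assigns an intervention domain only to participants with a documented matching risk, so improvement on a given scale may be concentrated in a minority.

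The second issue is precision. If change differs between centers, a paired test that treats all participants as independent gives intervals that are too narrow. The promise that clustering will be addressed is not carried through to these four outcomes.

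**Working it through.** **Inputs from the article.** 300 enrolled; 270, 255 or 240 evaluable after 10, 15 or 20% loss (2.14); 15 centers (2.1). No SDs, score ranges, MBI step size or intraclass correlation are given. Everything below that needs them is an assumption.

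**1. The plan's own precision figures.** Half-width = 1.96 × √(0.25/n). For n = 300, 270, 255 and 240 this gives 5.66, 5.96, 6.14 and 6.33 percentage points, matching the stated 5.7, 6.0, 6.1 and 6.3. These concern proportions; no precision is stated for the change scores.

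**2. How far mean and pseudo-median separate.** Assume that 80% of change scores follow N(0, 3) and 20% follow N(d, s), with the second entry the SD. The mean is 0.2d. The pseudo-median t solves

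0.64 Φ(t√2/3) + 0.32 Φ((t − d/2) / (½√(9 + s²))) + 0.04 Φ((t − d)√2/s) = 0.5.

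| d | s | Mean | Pseudo-median | Shortfall |
|---|---|---|---|---|
| 4 | 3 | 0.80 | 0.75 | 6% |
| 6 | 3 | 1.20 | 1.06 | 12% |
| 6 | 6 | 1.20 | 0.80 | 34% |
| 15 | 6 | 3.00 | 1.52 | 49% |

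The tests separate too. For a skewed change (exponential minus 1) with mean exactly 0 and 240 pairs, simulation gave 5.5% rejection for the t test and 71% for the signed-rank test. The pseudo-median there is −0.16, so the two tests are answering different questions.

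**3. Whether the t interval needs a normality check.** In the most skewed mixture above (d = 15, s = 6, rounded to integers), two simulations of 5,000 samples of 240 gave 95.0% and 94.6% coverage of the mean. At 60 pairs coverage was 94.5%. On coarse, symmetric integer changes (SD 1) the t test's type I error was 5.0% at 60 pairs and 4.5% at 240.

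**4. What Shapiro–Wilk would do.** Rejection rates at the 5% level for rounded normal change scores (1,000 runs each):

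| SD | n = 60 | n = 120 | n = 240 |
|---|---|---|---|
| 2 | 49% | 98% | 100% |
| 3 | 15% | 34% | 93% |
| 4 | 10% | 15% | 39% |
| 6 | 5% | 9% | 13% |
| 10 | 7% | 6% | 7% |

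The result depends on SD and number of pairs, neither of which the article gives for these scales.

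**5. Center.** With 240 pairs in 15 equal centers, m = 16 and the design effect is 1 + 15 × ICC, where ICC is that of the change score. The correct interval is √DE times as wide. The expected type I error of the unadjusted t test is about 2[1 − Φ(1.96/√DE)].

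| Assumed ICC | DE | Width ratio | Type I error, formula | Simulated |
|---|---|---|---|---|
| 0.01 | 1.15 | 1.07 | 6.8% | 6.3% |
| 0.02 | 1.30 | 1.14 | 8.6% | 8.8% |
| 0.05 | 1.75 | 1.32 | 13.8% | 14.1% |
| 0.10 | 2.50 | 1.58 | 21.5% | 21.6% |

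A t test on the 15 center means stayed at 5.0 to 5.5% in the same simulations. The signed-rank test behaves like the unadjusted t test (23.5% at ICC 0.10).

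**The case against.** Several points on the other side stand.

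- **Normality check.** A reader might infer that Shapiro–Wilk will nearly always reject on integer, bounded scales and so force the signed-rank test. The article does not support this. Shapiro–Wilk only supplements the plots, nocturia is an average rather than an integer, and the rejection rates in step 4 run from 7 to 100% at 240 pairs. What remains is that a plot judgement without a threshold leaves the choice discretionary.
- **Size of the divergence.** The halving needs one extreme, invented mixture. For symmetric changes the two estimates nearly coincide.
- **Number of pairs.** The figure of 240 is an evaluable count for a proportion. OABSS and POMA are given only when applicable (2.7), so their pair counts may be smaller. The t interval still holds up at 60 pairs in step 3, but the design effect shrinks with fewer pairs per center.
- **Center.** A reader might say that the plan ignores center. It does not: sections 2.14 and 2.15 provide for it. The defect is only that this provision has an undefined trigger and is not linked to the paired tests. Stable differences in level between centers also cancel in a change score, so the relevant ICC could be near the low end of the range.
- **Unpaired participants.** A reader might infer that everyone with a single measurement should be put into a mixed model. That conflicts with sections 2.7 and 2.12.2, which restrict OABSS and POMA to participants for whom the instrument applies and keep protocol-defined non-administration separate from missing data.
- **Status.** These outcomes are secondary and exploratory, and a statistical analysis plan not shown here may name the summary. However, the article does not leave the matter open. It states a rule, and a plan that follows the rule inherits the problem.

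**Conclusion.** The point holds in limited form. The stated rule lets the data decide whether a mean change or a pseudo-median is reported for four of six secondary outcomes, and the normality check behind it is not needed for the mean. The consequence ranges from slight under modest skew to about half the estimate in an extreme mixture.

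Neither test accounts for center. Intervals would need to be about 1.07 to 1.58 times as wide if the change-score ICC lies between 0.01 and 0.10. That range is assumed, as are equal center sizes and 240 pairs.

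The primary outcome is unaffected and no causal claim rests on these analyses. The priority is moderate to low, but the correction is cheap and recruitment had not begun at the stated trial status date.

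**What to change.** In section 2.15:

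1. Name the mean within-participant change with a 95% confidence interval as the estimate for OABSS, nocturia, POMA and MBI.
2. Compute it with center accounted for: a center random intercept on the change score, or a center-clustered standard error with a small-sample correction suited to 15 centers. Say that this applies to these four outcomes, so that the undefined trigger no longer matters here.
3. Remove the distribution-based choice of test. Keep median (IQR) as description and, at most, the signed-rank test with the Hodges–Lehmann estimate as a named sensitivity analysis.
4. Optionally, add a mixed model on baseline and Month 6 values as a sensitivity analysis for missing data, limited to participants for whom the instrument is still applicable and excluding protocol-defined non-administration.

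The cost is two or three sentences and no new data or sample size change. The intervals may be somewhat wider than those from the unadjusted tests.

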### 2.11. Follow-Up, Fall Ascertainment, and Dynamic Adjustment

Participants will be followed for 6 months using a standardized fall surveillance schedule across all centers, with structured contacts at Months 1, 2, 3, 4, and 5 and a final assessment at Month 6. Contacts may be conducted in person, by telephone, or by video according to accessibility; however, the surveillance interval, core questions, fall definitions, and event documentation procedures will be identical across centers. Additional clinical contacts may occur according to need but will not replace the scheduled surveillance.

The 6-month period was selected a priori to balance clinically meaningful prospective observation with feasibility in a multicenter implementation study. It permits estimation of 6-month toileting-related fall occurrence together with short-term changes in urinary symptoms, nocturia, mobility, functional independence, fidelity, safety, and follow-up performance. The monthly structured surveillance is intended to reduce recall-related underreporting; the study is not designed to establish long-term preventive effectiveness, recurrent fall risk beyond follow-up, or long-term organizational sustainability.

At enrollment, participants and/or caregivers will be instructed to record and promptly report any fall during follow-up. At each monthly contact, investigators will use a standardized surveillance form to determine whether a fall occurred since the previous contact and will document the date; relationship to going to, using, transferring on or off, or returning from the toilet; nighttime occurrence; location and circumstances; resulting injury; and assistance available at the time.

A fall is an event in which a participant unintentionally comes to rest on the ground, floor, or another lower level. Toileting-related falls will use the prespecified primary outcome definition. Caregivers may assist in reporting when participants cannot report reliably. Events reported between scheduled contacts will be reconciled at the next contact to avoid duplication.

Missed monthly contacts will be completed as soon as feasible and documented. At Month 6, all fall records will undergo a final completeness and classification review.

Care plans may be modified for new risks, symptom change, poor adherence, adverse events, or changes in function or care environment; major modifications and reasons will be documented.

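### The one stated missing-data sensitivity analysis for the primary outcome discards fall-free follow-up time, so at the highest loss scenario its valid bounds are too wide to be useful

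*Protocol article*

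**What the plan says.** Section 2.12.1 defines the primary outcome as "the proportion of participants with ≥1 such fall among those with an evaluable 6-month outcome status". Under section 2.15, a participant who has a documented toileting-related fall and is then lost stays event positive. A participant lost without such a fall has incomplete status, however long the fall-free observation lasted.

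For these incomplete participants, section 2.15 states a single sensitivity analysis: "extreme-case sensitivity bounds will alternatively classify participants with incomplete 6-month status and no prior documented toileting-related fall as event positive or event negative".

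Surveillance under section 2.11 consists of "structured contacts at Months 1, 2, 3, 4, and 5 and a final assessment at Month 6", and the date of each fall is recorded. The data therefore show when each fall happened and up to which contact each lost participant was known to be fall-free. In section 2.15, follow-up time enters only the rate models for nighttime toileting-related falls and total falls, as an offset.

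Section 2.14 sets enrolment at 300 and illustrates loss: "With a 10%, 15%, or 20% loss to follow-up, approximately 270, 255, or 240 participants would remain evaluable". These are three scenarios for precision. The article does not plan on any one of them.

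**The concern.** The two extreme assignments use one fact about each lost participant: whether a toileting-related fall was documented before loss. How much of the six months was actually unobserved plays no part. One missing month and six missing months carry the same weight, although the first leaves far less room for an unseen fall.

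The width of the bounds is therefore set mainly by the loss rate. At higher loss a reader gets a wide range with no guidance on where in it the incidence plausibly lies. The bounds also cannot show a smaller and more likely problem. In the evaluable-only proportion, lost participants enter the denominator only if they fell, which moves the estimate upward even when loss has nothing to do with falling. Estimating this incidence is the primary clinical objective (section 2.2), so the sensitivity analysis should be able to inform it.

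**Working it through.** **1. The article's own precision figures.** Half-width = 1.96 × √(0.25/n). For n = 300, 270, 255 and 240 this gives 5.66, 5.96, 6.14 and 6.33 points. Section 2.14 states 5.7 for 300, and for the three loss scenarios "maximum 95% confidence interval half-widths of about 6.0, 6.1, or 6.3 percentage points for a proportion near 50" per cent. The figures reproduce. They are half-widths, so the full interval near 50% is about 11 to 13 points.

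**2. Width of the bounds from the article's counts.** Width = (lost without a prior event)/300. Counting everyone lost as incomplete, as section 2.14 does:
- 10% loss: 30/300 = 10 points
- 15% loss: 45/300 = 15 points
- 20% loss: 60/300 = 20 points

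**3. Width allowing for falls before loss.** The article gives no expected incidence or timing of loss. Assume a 6-month risk p, a constant hazard, and loss of a fraction d spread evenly over 0 to 6 months and unrelated to falling. With H = −ln(1 − p), the mean probability of being fall-free at loss is p/H.
- Width = d × p/H
- Lower bound = (1 − d)p + d(1 − p/H)
- Upper bound = lower bound + width

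For p = 0.20 and d = 0.20: H = 0.2231 and p/H = 0.896.
- Incomplete: 300 × 0.20 × 0.896 = about 54
- Width: 17.9 points
- Lower bound: 0.160 + 0.0207 = 18.1%
- Upper bound: 36.0%

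| Assumed 6-month risk | Bounds width, 20% loss | Full 95% CI width, 20% loss | Bounds width, 10% loss | Full 95% CI width, 10% loss |
|---|---|---|---|---|
| 10% | 19.0 | 7.9 | 9.5 | 7.3 |
| 20% | 17.9 | 10.4 | 9.0 | 9.6 |
| 30% | 16.8 | 11.6 | 8.4 | 11.0 |
| 40% | 15.7 | 12.2 | 7.8 | 11.6 |
| 50% | 14.4 | 12.2 | 7.2 | 11.7 |

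The CI is for the planned evaluable-only proportion. At 20% loss the bounds are wider than the sampling interval at every risk examined. At 10% loss they are narrower, except at a risk of 10%.

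**4. What fall-free time is worth.** Take p = 0.20 and a hazard equal to the observed one. A participant lost on day 1 has a 20% chance of a fall in the unobserved period. One lost after five fall-free months has 1 − 0.8^(1/6) = 3.6%, and 1 − 0.8^(3/6) = 10.6% at three times the hazard. The upper bound assigns 100% to both.

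**5. Imputing only the unobserved months.** Let u be the fraction of the six months observed before loss, uniform on 0 to 1. With the hazard after loss set to k times the observed one, incidence = (1 − d)p + d × {1 − mean of exp[−Hu − kH(1 − u)]}. For p = 0.20:

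| Loss | k = 0.5 | k = 1 | k = 2 | k = 3 | Extreme bounds |
|---|---|---|---|---|---|
| 20% | 19.1% | 20.0% | 21.7% | 23.1% | 18.1% to 36.0% |
| 10% | 19.5% | 20.0% | 20.8% | 21.6% | 19.0% to 28.0% |

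At 20% loss, k from 0.5 to 3 moves the estimate by 4 points, against 18 for the bounds.

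**6. The planned proportion on the same scale.** At p = 0.20 and d = 0.20, the evaluable-only proportion has expectation 18.07/(100 − 17.93) = 22.0%. This is 2 points above the assumed true risk although loss is unrelated to falling, and it lies between k = 2 and k = 3. In 2,000 simulated cohorts of 300 under these assumptions, the Kaplan-Meier estimate averaged 20.1% and the evaluable-only proportion 22.1%. Bounds of 18.1% to 36.0% contain both values and cannot separate them.

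**The case against.** The strongest reply is that nothing in section 2.15 is wrong. Extreme-case bounds are legitimate limits for a binary outcome with unknown status and need no assumption about why people were lost. That stands, and the bounds should stay. The outcome is also exploratory, with no test or threshold resting on it, which limits the stakes.

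A second reply is that the article refers to a separate statistical analysis plan, which is not shown and may hold further scenarios. That also stands: the point concerns what the article states, and the absence of a further analysis there is not an error in itself.

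Four stronger readings are tempting, and the documents do not support them.
- A reader might infer that the monthly contacts are ignored. Falls found at those contacts before loss are counted; only the fall-free time is unused.
- A reader might take 20% as the planned loss. It is the largest of three illustrative rates.
- A reader might set an 18-point range against the stated 6 points and call it a threefold excess. The 6 is a half-width near 50%. Against the full width of 10.4 points at 20% incidence and 20% loss, the ratio is about 1.7.
- A reader might conclude that the bounds can never show robustness. At 10% loss they are 7 to 10 points wide, comparable with or narrower than the confidence interval at most risks examined.

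The article also commits to completing missed contacts where feasible and to reporting reasons for loss. This helps, but it puts no size on the possible bias.

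**Conclusion.** The point holds as a modest improvement. The stated sensitivity analysis is valid but discards information the trial collects, and it offers nothing between its two extremes. The cost depends on loss. At 20% the bounds span 20 points on the article's counts, or about 14 to 19 points once falls before loss are allowed for; at 10% they remain informative. The 14-to-19 range rests on an assumed incidence of 10% to 50%, a constant hazard and evenly spread loss unrelated to falling, none of which the article supplies. On the same assumptions, with 20% incidence and 20% loss, using fall-free time narrows the plausible range to about 4 points for k between 0.5 and 3. It also exposes an upward shift of about 2 points in the planned proportion, which the bounds cannot reveal.

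**What to change.** Keep the extreme bounds as outer limits. Add a prespecified sensitivity analysis that uses each participant's observed fall-free time up to the last completed contact and imputes only the unobserved months. Set the toileting-fall hazard there to k times that of comparable observed participants, for example k = 0.5, 1, 2 and 3. The k = 1 case is equivalent to a time-to-first-fall (Kaplan-Meier type) 6-month cumulative incidence. Report the estimate for each k beside the primary proportion.

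The cost is a short paragraph in the analysis plan, a little more programming, and a choice of k values, which is a judgement and should be fixed before data are seen. No new data are needed. Section 2.18 says recruitment had not begun as of 1 August 2026, so prespecification was still possible at that date.
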